## LIST OF ABBREVIATIONS

| Abbreviation | Description                                             |
|--------------|---------------------------------------------------------|
| ACB          | Aortocoronary Bypass                                    |
| ADR          | Adverse Drug Reaction                                   |
| AE           | Adverse Event                                           |
| ALT          | Alanine Aminotransferase                                |
| AST          | Aspartate Aminotransferase                              |
| BMI          | Body Mass Index                                         |
| CI           | Confidence Interval                                     |
| CPB          | Cardiopulmonary Bypass                                  |
| CRF          | Case Report Form                                        |
| CRO          | Contract Research Organization                          |
| E-CABG       | European Coronary Artery Bypass Grafting                |
| eCRF         | Electronic Case Report Form                             |
| EDC          | Electronic Data Capture                                 |
| EXTEM        | ROTEM Assay Assessing the Extrinsic Coagulation Pathway |
| GCP          | Good Clinical Practice                                  |
| HIV          | Human Immunodeficiency Virus                            |
| IABP         | Intra-Aortic Balloon Pump                               |
| ICU          | Intensive Care Unit                                     |
| IDSMC        | Independent Data Safety Monitoring Committee            |
| IMP          | Investigational Medicinal Product                       |
| INR          | International Normalized Ratio                          |
| ITT          | Intention-To-Treat                                      |
| MCF          | Maximum Clot Firmness                                   |
| IV           | Intravenous                                             |
| MedDRA       | Medical Dictionary for Regulatory Activities            |
| OR           | Operating Room                                          |
| PCC          | Prothrombin Complex Concentrate                         |
| POD          | Postoperative Day                                       |
| PP           | Per-Protocol                                            |
| PRV          | Pseudorabies Virus                                      |
| PT           | Prothrombin Time                                        |
| PTT          | Partial Thromboplastin Time                             |
| RBC          | Red Blood Cell                                          |
| REB          | Research Ethics Board                                   |
| rFVIIa       | Recombinant Activated Factor VII                        |
| SAE          | Serious Adverse Event                                   |
| SAF          | Safety Analysis Population                              |

| Abbreviation | Description                                    |
|--------------|------------------------------------------------|
| SBV          | Schmallenberg Virus                            |
| SDM          | Surrogate Decision Maker                       |
| SDV          | Source Data Verification                       |
| TACS         | Transfusion Avoidance in Cardiac Surgery       |
| TEAE         | Treatment Emergent Adverse Event               |
| TEE          | Thromboembolic Event                           |
| UDPB         | Universal Definition of Perioperative Bleeding |
| WFI          | Water for Injections                           |

## 1 INTRODUCTION

### 1.1 Background

#### Bleeding in cardiac surgery

Cardiac surgery is frequently complicated by coagulopathic bleeding that often leads to excessive blood loss, blood product transfusion and bleeding-related complications (5-8). Bleeding and transfusions are associated with increased morbidity and mortality, including up to an 8-fold increase in the odds of death (6), and patients with major bleeding are at particularly high risk of adverse outcomes (e.g., infection, heart failure, and mortality) (9-21).

Coagulopathy during cardiac surgery is caused by several factors, including the contact of blood with the cardiopulmonary bypass (CBP) circuit, which activates the intrinsic and extrinsic coagulation pathways (despite the use of heparin and heparin-coated circuits), causing excessive clot formation and breakdown. Other contributory factors include hemodilution, hypothermia, blood loss, surgical trauma, and use of foreign substances such as aortic grafts causing the consumption of coagulation factors (22-26). These in turn can lead to excessive fibrinolysis and fibrinogen deficiency, platelet dysfunction and thrombocytopenia (24, 25). Deficiency of enzymatic coagulation factors (e.g., vitamin K-dependent factors II, VII, IX, X, and XI) is also an important cause of coagulopathy, leading to impaired generation of thrombin, which is considered to be central in the coagulation cascade (27, 28). Activated thrombin converts soluble fibrinogen into insoluble strands of fibrin, which forms the basis of the clot, and it catalyzes numerous other coagulation-related reactions (29); consequently, replacement of coagulation factors is an important aspect of a multimodal approach to coagulopathy to reduce bleeding and transfusion (8, 30).

To replenish depleted coagulation factors and improve thrombin generation, two therapeutics, frozen plasma (FP) and prothrombin complex concentrate (PCC), are available. FP is currently the mainstay of therapy for patients with acquired coagulopathies in North America whereas PCC is the mainstay of therapy in much of Europe (31).

#### Frozen Plasma

FP is obtained from donated whole blood and contains all enzymatic coagulation factors, although some coagulation factor activity is lost during storage and processing (including freezing for storage and thawing prior to transfusion) (32). FP utilized in North America is not pathogen-reduced. FP is the mainstay of therapy for bleeding cardiac surgery patients requiring coagulation factor replacement in many countries, and is administered in around 15% of all cardiac surgeries in the United States (33). Despite being a mainstay of therapy, there is no clinical trial evidence for the use of FP in bleeding cardiac surgery patients requiring coagulation factor replacement. A systematic review investigating the use of FP identified only one study that tested the interventional (i.e., not prophylactic) use of FP in patients undergoing cardiac surgery (34). In this study, two types of FP were compared but a randomized control group was not included, making it difficult to draw conclusions about the efficacy and safety of FP (35). When also considering trials that tested FP prophylactically, the authors concluded that there is no evidence for the efficacy of FP in the prevention of bleeding for patients undergoing cardiac surgery but some evidence for an increase in RBC transfusion in those treated with FP. Moreover, in a prospective cohort study of 967 patients undergoing cardiac surgery, FP transfusion was not associated with improved 30-day mortality rates (36).

The lack of evidence for the efficacy of FP is concerning in the context of the risks associated with its use (37, 38). FP can lead to adverse events (AEs) including allergic reactions in 1–3% of transfusions, and while most are not serious, life-threatening anaphylaxis can occur (34). Transfusion-related acute lung injury (TRALI) is associated with plasma-containing components and is a leading cause of transfusion-related death (34, 39). Also, transfusion-associated circulatory overload (TACO), which occurs as a result of the large volume of transfusion required to achieve therapeutic effect with FP, occurs in approximately 5% of transfusions and is fatal in 2% (40). FP transfusion is associated with transmission of infectious diseases, as FP is not usually filtered or treated with solvent/detergent (41). These adverse effects are often dose dependent (42–45). FP requires ABO blood group compatibility matching and thawing, which can delay therapy. The large volumes of FP needed to effectively raise thrombin generation can further delay time to hemostatic control and lead to substantial hemodilution, resulting in additional RBC transfusions (46).

#### Prothrombin Complex Concentrate

PCC offers a potential alternative to FP for treating bleeding cardiac surgery patients requiring coagulation factor replacement. PCCs contain prothrombin and other enzymatic coagulation factors, the anticoagulant proteins C and S and anti-thrombin, and small amounts of heparin; they are routinely defined as 3-factor (that contain factors II, IX, and X) or 4-factor (that contain factors II, VII, IX, and X) formulations (47). PCCs are purified from human pooled plasma, which is fractionated into cryoprecipitate and cryoprecipitate-free plasma fractions through a process of slow thawing, then eluted from cryoprecipitate-free plasma (47). The production of PCCs includes strict viral inactivation using solvents, detergents, pasteurization, nanofiltration, and vapor-heated treatment (5, 47).

PCCs have several potential advantages over FP. Solvent/detergent treatment and filtering to remove viruses substantially reduces the risk of transmission of infectious agents with PCCs. Indeed, a Consensus Conference recommended in 2007 that pathogen reduction technologies should be implemented to improve the safety of transfusion when they became available (48). Unlike FP, PCCs do not require ABO compatibility matching or thawing, and can therefore be prepared and administered more quickly. PCCs are associated with a substantially lower risk of TRALI (due to pooling of the source donor plasma), and also a lower risk of TACO (37), as substantially lower volumes of PCC are required than with FP to achieve dose-equivalence for increasing thrombin generation (for example, in a 70-kg patient, a standard dose of 25 IU/kg PCC would be administered in a volume of 80 mL, whereas a standard dose of 15 mL/kg FP would be administered in a volume of 1000 mL) (46). PCCs contain standardized levels of coagulation factors and thus have a more predictable therapeutic effect than FP, whose coagulation factor concentrations vary depending on the characteristics of the donor (49, 50).

PCCs do not contain the full balanced complement of procoagulants and anticoagulants present in FP (51) and it is therefore conceivable that they might be less effective, although *in vitro* studies suggest that PCCs may be more effective than FP in enhancing thrombin generation after cardiac surgery (46). Also, because PCCs contain more procoagulants than anticoagulants, they may carry a higher risk of thrombotic events, disseminated intravascular coagulation and acute kidney injury (47, 52–56). Finally, since PCCs contain heparin, they are contraindicated in patients who are allergic to heparin or have a prior history of heparin induced thrombocytopenia.

### Review of the literature

Few guidelines exist on the use of PCC in acquired coagulopathies. The European Society of Anaesthesiology recommends goal-directed therapy with coagulation factor concentrates, including PCC, since this may reduce transfusions during cardiac surgery (57), and the American Society of Anesthesiologists suggests PCCs for excessive bleeding in the presence of elevated INR (58). However, there is little high-quality clinical evidence to support these recommendations: there are few direct comparisons of PCC versus FP for managing coagulopathy resulting from coagulation factor deficiency during cardiac surgery (or other types of surgery) and randomized controlled trials have not yet been performed.

We carried out an observational study that compared outcomes for patients at Toronto General Hospital who received FP ( $n=1151$ ), PCC ( $n=79$ ), or both ( $n=125$ ) for management of coagulopathy after cardiac surgery between 2012 and 2016 (59). Using propensity score matching, we matched 117 patients who received FP with 117 patients with similar risk and surgery profiles who received PCC (with or without FP). (As part of the Risk Factor Validation study [REB#: 16-5649]. The odds ratio (OR) for red cell transfusion avoidance was 2.4-fold (95% confidence interval [CI] 1.2–4.8) higher for patients receiving PCC. In addition, incidences of massive transfusion (OR 0.58; 95% CI 0.33–1.0) and refractory bleeding (OR 0.49; 95% CI 0.24–1.03) tended to be lower in patients who received PCC. Results from this exploratory study suggest that PCC is potentially more efficacious than FP in avoiding transfusion, and AE profiles were similar between groups, suggesting a comparable safety profile.

Our results are similar to those from other studies. A recent systematic review only identified 4 small, non-randomized studies – including our own (59) – comparing perioperative PCCs to FP in cardiac surgery (60). The meta-analysis showed PCCs were associated with reduced risk of RBC transfusion (OR 2.22; 95%CI 1.45-3.40) and fewer units of RBCs transfused (OR 1.34; 95%CI 0.78-1.90). PCCs were not associated with increased hospital mortality (OR 0.94; 95%CI 0.59-1.49), stroke (OR 0.80; 95%CI 0.41-1.56) or AKI occurrence (OR 0.80; 95%CI 0.58-1.12), suggesting that PCCs are more effective than FP without decreasing safety. In one of the studies in the systematic review, Arnekian and colleagues (61) compared three groups of cardiac surgical patients: 24 who received only PCC, 26 who received only FP, and 27 who received both products. In an unadjusted analysis, they found that RBC transfusions occurred least frequently in the PCC group and most frequently in patients who received both products. However, given the small sample size and lack of risk-adjusted analysis, few conclusions can be drawn from this study. In another study that included only patients who underwent pulmonary endarterectomy with cardiopulmonary bypass (CPB), Ortmann and colleagues (62) compared transfusion requirements and outcomes between 55 patients who received only FP and 45 patients who received only PCC for management of post-CPB coagulopathic bleeding. In an unadjusted analysis, they found that the PCC group had lower blood loss than the FP group, but transfusion rates were similar. They conducted multivariable regression analysis for AEs and found no differences between the two groups. However, given its small sample size, limited generalizability, and lack of risk-adjustment for efficacy outcomes, this study should be interpreted with caution. In a larger study, Cappabianca and colleagues (63) used propensity scores to match 225 patients who received PCC (with or without FP) to 225 patients who received only FP for management of post-CPB coagulopathy. They found that RBC transfusion requirements were lower in the PCC group (84% versus 93%), as were multiple (more than two units) RBC transfusions (51% versus 70%) and number of units of RBCs transfused (3.4 versus 5.2 units). While there were no major between-group differences in adverse outcomes, in a regression analysis that incorporated the propensity score the authors noted an association between PCC use and acute kidney injury that led them to caution about this potential risk. Similarly, in a recent multi-centre observational study not included in the above systematic

review, Biancari and colleagues compared 101 patients who received FP following coronary artery bypass grafting to 101 propensity-score-matched patients who received PCC with or without FP (64). PCC was associated with a significant decrease in rate of RBC transfusions (67.3% vs. 83.2%), but was also associated with an increased risk of acute kidney injury. However, there were many limitations to this study, including unknown differences in PCC dosage, bleeding severity and coagulopathy. Furthermore, in the group of patients that received both FP and PCC, it was not known what the order of administration was and so PCC could have been given as salvage therapy (64). Together, these studies suggest that PCC may be more efficacious than FP in cardiac surgery; however, data from well-designed, prospective, randomized trials are lacking.

## 1.2 Rationale for Conducting the Study

The proposed pilot study will determine the feasibility, and inform the design and primary outcome parameter, of a definitive Phase 3 trial comparing the efficacy and safety of the PCC *Octaplex* versus FP in bleeding cardiac surgical patients in whom coagulation factor replacement with PCC or FP is ordered according to accepted clinical standards. In addition, the results from the pilot study will be used in sample size calculations for the full study and safety data will be compared to detect any early safety issues. A better homogeneity of the study cohort can be expected if only a single PCC, rather than any registered PCC, is admitted for comparison.

The primary objective of the potential future Phase 3 study will be to determine if PCC is non-inferior or superior to FP in terms of efficacy and safety in consecutive bleeding cardiac surgical patients in whom coagulation factor replacement (with PCC or FP) is ordered according to accepted clinical standards. By using a randomized controlled design and multiple centres to increase generalizability and statistical power to detect differences in adverse events, the confirmative Phase 3 study will address many of the limitations of previous studies.

Hemostatic management in bleeding surgical patients is evolving from empirical therapy with non-purified allogeneic blood products to targeted therapy with purified products that have undergone treatment with pathogen reduction technologies (65). The proposed study, by comparing two currently available but distinctly different therapies for treating bleeding surgical patients requiring coagulation factors, is well aligned with this change. Given the potential advantages of PCC over FP detailed above (viral inactivation, ease of administration, standardized dosing/predictable effect, and substantially lower risk of TRALI and TACO due to smaller volume), we believe that a finding of superiority or non-inferiority will lead to the use of PCC in place of FP for the management of bleeding surgical patients requiring coagulation factor replacement.

## 1.3 Benefit-Risk Statement

Substituting either PCC or FP for the other is not expected to pose any material risks to the participants. Patients will only be included in the trial when their clinicians have ordered coagulation factor replacement for treatment of bleeding, according to accepted clinical standards. The two coagulation factor replacement therapies, *Octaplex* (the PCC to be used in this study) and FP, are currently within the standard of care for this procedure. *Octaplex* is currently approved for use in Canada for the “treatment of bleeding and perioperative prophylaxis of bleeding in acquired deficiency of prothrombin complex coagulation factors, such as deficiency caused by treatment with vitamin K antagonists, or in case of overdose of vitamin K antagonists, when rapid correction of the deficiency is required” (66). Neither *Octaplex* nor FP pose additional risks to patients and

entail no additional interventions outside of normal clinical care. No patient will receive coagulation factor replacement solely for the purposes of this study.

The experience to date with this PCC has shown an excellent safety profile (67-71). As discussed, PCC is pathogen reduced, can be administered quickly and in predictable doses, and has a substantially lower risk of TRALI and TACO compared with FP, making its administration likely to be both safer than, and at least as efficacious as, FP. It is possible that treatment with PCC may not be as effective as FP given that it does not contain the full complement of clotting factors that plasma contains. By limiting maximal PCC dosing to well within acceptable limits that have been proven safe in other settings (67-71), we are confident that the potential risk of thrombotic complications has been addressed.

#### **1.4 Principal Investigator (Sponsor)**

The Sponsor and Coordinating Investigator of this study is [name] at the Department of Anesthesia and Pain Management, Toronto General Hospital, [name].

Octapharma AG will support the conduct of this study by awarding an unrestricted grant for study conduct, supporting data management and statistical services.

## **2 STUDY OBJECTIVES**

The main objective of this pilot trial is to inform the design and primary outcome parameter for a definitive Phase 3 trial comparing the efficacy and safety of PCC (*Octaplex*) versus FP in bleeding cardiac surgical patients in whom coagulation factor replacement with PCC or FP is ordered according to accepted clinical standards.

### 3 INVESTIGATIONAL PLAN

#### 3.1 Endpoints

This pilot study aims to select a clinically relevant primary efficacy endpoint for a confirmative Phase 3 study.

##### 3.1.1 Efficacy Endpoints

###### *Primary Endpoints:*

1. Treatment response, defined as effective if no additional hemostatic intervention (such as administration of hemostatic agents including a second dose of IMP, platelet transfusion, or surgical re-exploration) from 60 minutes to 4 and 24 hours after initiation of the first dose of IMP (otherwise will be defined as not effective). If the dose of IMP is repeated within less than 60 minutes, treatment response to the IMP will be assessed for the 60 minutes after the second IMP dose only.
2. Amount of allogeneic blood products (for each type of product and cumulatively) administered during the first 24 hours after the start of surgery.
3. Number of patients who do not receive any RBC transfusions or any allogeneic blood transfusions during the first 24 hours after the start of surgery.

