#### 4.2.1 Permitted Concomitant Therapy

Participating hospitals will use a standardized point-of-care based transfusion algorithm that will employ a targeted approach to correct coagulopathy (as per the validated TACS algorithm) (4), but with selection of PCC or FP determined according to the patient's assigned grouping and using the doses described in **Section**

**3.3.2.** Recommended RBC transfusion thresholds will be 75 g/L during surgery and 85 g/L in bleeding or unstable patients.

Concomitant administration of any therapies required as part of standard patient care is permitted but must be recorded in the CRFs. All hemostatic drugs or products administered (e.g., heparin and protamine dose, anti-fibrinolytic drugs, desmopressin, rFVIIa, idarucizumab, andexanet alpha, or topical hemostatic agents) will be recorded, as well as all procedures that may influence amount of bleeding (e.g., retrograde autologous priming of CPB circuit, cell salvage). In addition, concomitant medications used to treat SAEs will be reported throughout the duration of follow-up (up to POD-28).

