#### **7.2.2 Transfusion Data**

Details of all blood products and hemostatic agents released from the blood bank and transfused will be collected from the blood bank databases. These include allogeneic blood products (RBCs, pooled or apheresis platelets, and plasma) and albumin. Other hemostatic agents include: desmopressin, fibrinogen concentrates, rFVIIa, idarucizumab, and andexanet alpha.

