#### 4.6 Efficacy

The primary population for the analysis of the efficacy of the IMPs will be the ITT. The primary efficacy endpoints will also be analyzed for the PP population.

The analysis of efficacy will focus on the following primary endpoints:

P1. Treatment response, defined as effective if no additional hemostatic intervention (such as administration of hemostatic agents including a second dose of IMP, platelet transfusion, or surgical re-exploration) in the time windows

- from 60 minutes to 4 and 24 hours after initiation of the first dose of IMP,
- *from initiation of the first dose of IMP to 4 and 24 hours.*

Otherwise, treatment response will be considered as not effective, see section 6.1. If the dose of IMP is repeated within less than 60 minutes, treatment response to the IMP will be assessed for the time frames after the second IMP dose only.

P2. Amount of allogeneic blood products (for each type of product and cumulatively) administered

- during the first 24 hours after the start of surgery,
- *during the first 24 hours after the end of CPB,*
- *during the first 24 hours after randomization,*
- *during the first 24 hours after the start of first IMP dose.*

P3. Number of patients who do not receive any allogeneic blood product (in total and for each type separately)

- during the first 24 hours after the start of surgery,
- *during the first 24 hours after the end of CPB,*
- *during the first 24 hours after randomization,*
- *during the first 24 hours after the start of first IMP dose.*

In addition the following efficacy endpoints will be explored:

S1. Number of partial or full IMP doses of PCC and FP administered

- during the first 24 hours after the start of surgery.
- *during the first 24 hours after the end of CPB,*
- *during the first 24 hours after randomization,*
- *during the first 24 hours after the start of first IMP dose.*

|                           |                 |             |               |
|---------------------------|-----------------|-------------|---------------|
| Statistical Analysis Plan | Version 2.0     |             | Page 13 of 19 |
| Sponsor                   | [name] | Protocol No | FARES         |

S2. Incidence of major bleeding, using the universal definition of perioperative bleeding (UDPB) in cardiac surgery scores and their individual components

- during the first 24 hours after start of surgery,
- *during the first 24 hours after the end of CPB,*

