## 6 DERIVATIONS AND TRANSFORMATIONS

### 6.1 Formulas for derived variables

| Variable                               | Definition / Derivation                                                                                                                                                                                                                                                                                                                                                                                                                                                                            |
|----------------------------------------|----------------------------------------------------------------------------------------------------------------------------------------------------------------------------------------------------------------------------------------------------------------------------------------------------------------------------------------------------------------------------------------------------------------------------------------------------------------------------------------------------|
| Response (4h)
(Treatment response)  | 
= 'Effective' ('Yes') if no additional hemostatic intervention occurred (such as administration of hemostatic agents including a second dose of IMP, platelet transfusion, or surgical re-exploration) from 60 minutes to 4 hours after initiation of the first dose of IMP.
 
= 'Ineffective' ('No') otherwise.
 
If the dose of IMP is repeated within less than 60 minutes, treatment response to the IMP will be assessed for the 60 minutes after the second IMP dose only.
  |
| Response (24h)
(Treatment response) | 
= 'Effective' ('Yes') if no additional hemostatic intervention occurred (such as administration of hemostatic agents including a second dose of IMP, platelet transfusion, or surgical re-exploration) from 60 minutes to 24 hours after initiation of the first dose of IMP.
 
= 'Ineffective' ('No') otherwise.
 
If the dose of IMP is repeated within less than 60 minutes, treatment response to the IMP will be assessed for the 60 minutes after the second IMP dose only.
 |

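### Treatment response (P1 and S9) has no rule for death, so a patient who dies in the window without a further hemostatic intervention counts as a success; the list of failure events is also left open

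*Combined protocol and SAP*

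**What the plan says.** Protocol 3.1.1 makes treatment response the first primary endpoint: "Treatment response, defined as effective if no additional hemostatic intervention (such as administration of hemostatic agents including a second dose of IMP, platelet transfusion", with surgical re-exploration as the third example. The window runs "from 60 minutes to 4 and 24 hours after initiation of the first dose of IMP". SAP 4.6 repeats this as P1 and adds an exploratory window, "from initiation of the first dose of IMP to 4 and 24 hours". SAP 6.1 gives the derivation: effective if no such intervention occurred, and "Ineffective' ('No') otherwise".

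If the IMP is repeated within 60 minutes, P1 moves the assessment to the period after the second dose. S9, the conservative version added in SAP version 2.0, scores that patient not effective instead. Nothing else in the response definition changes.

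Two other protocol sections name hemostatic agents. Section 4.2.1, on concomitant therapy, says what is to be recorded: "All hemostatic drugs or products administered (e.g., heparin and protamine dose, anti-fibrinolytic drugs, desmopressin, rFVIIa", and further examples. Section 7.2.2, on data taken from the blood bank databases, says: "Other hemostatic agents include: desmopressin, fibrinogen concentrates, rFVIIa, idarucizumab, and andexanet alpha". Neither refers to the response endpoint.

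Death is analysed in the safety composite (protocol 3.1.2), as 28-day mortality (protocol 3.1.3), and by risk ratio and Kaplan-Meier estimates (SAP 4.7.1).

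**The concern.** Response is defined only by the absence of an event, and death stops that event from happening. Unless death is scored explicitly, the worst outcome can be recorded as the best one.

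This matters more here than in most pilots. The stated aim is to select the primary endpoint for Phase 3, and protocol 1.2 says that the pilot's results will feed the Phase 3 sample size. A definition that credits early deaths as successes would carry forward both a distorted rate and the flaw itself.

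The open list is a lesser problem of the same kind. SAP 6.1 is the section from which P1 is programmed, and it leaves whoever programs it to decide which agents count. Treating clinicians know the allocation once the seal is broken (protocol 3.3.7 and 5.2), so that decision should be fixed before unblinding.

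**Working it through.** The plan states no figure for this endpoint, so there is none to reproduce. The check applies the written rule to cases and then sizes the effect.

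**1. The rule.** As SAP 6.1 is written, response = effective if the number of additional hemostatic interventions in the window is 0, and ineffective if it is 1 or more. Vital status does not enter.

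**2. Hypothetical patients under the 60-minute window.**

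| Course after the first IMP dose | 4 h | 24 h |
|---|---|---|
| Alive, no further intervention | Effective | Effective |
| Alive, platelets at 3 h | Ineffective | Ineffective |
| Platelets at 2 h, dies at 3 h | Ineffective | Ineffective |
| No further product or re-exploration, dies at 3 h | Effective | Effective |
| No further product or re-exploration, dies at 30 min | Effective | Effective |

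The last patient is never observed inside the window and still meets the definition. Starting the window at the first dose changes neither of the last two rows, and neither does S9.

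**3. Is there a rule elsewhere?** SAP 4.1.2 says only that nothing is imputed, and protocol 9.2.3 says much the same. If one argued that a death makes the response missing, the patient would drop out of the denominator rather than count as a failure, and the SAP does not say even that. The mortality analyses do not alter the P1 score.

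**4. Can such a patient be in the analysis?** SAP 3.4 requires consent, at least one treatment with PCC or FP, and cardiac surgery. Protocol 10.3 provides for approaching next-of-kin up to two weeks after an early death. So yes, if that consent is given.

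**5. Size.** The expected evaluable number is 50 per arm (protocol 9.1; SAP 1.3). With d such deaths in an arm, the response rate is too high by d/50:
- d = 1: 1/50 = 2 points
- d = 2: 2/50 = 4 points
- d = 3: 3/50 = 6 points

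The between-arm difference shifts by (d1 − d2)/50. Equal numbers in the two arms inflate both rates and leave the difference unchanged. The documents give no basis for a value of d.

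**6. The failure list.**

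| Agent | Protocol 4.2.1 | Protocol 7.2.2 |
|---|---|---|
| Heparin, protamine | Named | Not named |
| Antifibrinolytics, topical agents | Named | Not named |
| Desmopressin, rFVIIa, idarucizumab, andexanet alpha | Named | Named |
| Fibrinogen concentrate | Not named | Named |
| Cryoprecipitate | Not named | Not named |

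Cryoprecipitate is nevertheless collected (Table 1) and is a component of the bleeding classification (Table 4). Of these agents, P1 itself names none.

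**The case against.** The case against the death point is that it will rarely arise. Patients in a critical state with a high probability of death within 24 hours are excluded (protocol 4.1.2), sites follow a transfusion algorithm, and further doses are available. A bleeding patient is likely to receive something that counts as failure before dying, and mortality is reported separately. All of this bears on frequency and stands as far as it goes. It does not change how such a patient is scored.

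On the list, the two protocol sections have different scopes: one covers all hemostatic drugs given, the other what the blood bank supplies. Their differences are therefore not a contradiction. The trial is exploratory, timing of products and agents is collected (protocol 6.1.2), and other definitions could be derived later. That lowers the stakes but leaves the primary definition unsettled.

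A reader might go further and infer three things that the documents do not support:
- **That routine protamine or antifibrinolytics make a patient a failure.** Section 4.2.1 is a recording rule with examples, and it names heparin as well, so it cannot sensibly be a list of failure events. Section 7.2.2 uses P1's own term and names neither drug. The word *additional* leaves room to exclude a continuing infusion, and in the protocol window nothing before 60 minutes counts.
- **That any return to theatre is a failure.** Re-exploration is given as an example of a hemostatic intervention, which already points to bleeding.
- **That counting routine agents would lower the response rate by a known amount.** The documents give neither a response rate nor a frequency of such use.

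**Conclusion.** The point holds for death. As written, P1 and S9 classify a consented patient who dies before 4 h or 24 h, with no additional hemostatic intervention in the window, as a treatment success. Each such patient adds 2 percentage points to an arm of 50. This assumes 50 evaluable patients per arm and a literal reading of SAP 6.1. The number of such deaths is unknown and may be zero, and no bias toward either arm is shown.

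The open list is a secondary gap. The documents leave undecided which agents count, and no size can be put on that from what they contain.

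**What to change.** **Death.** In SAP 4.6 and 6.1, for P1 and S9 and for every window, add: *Death before the end of the assessment window is classified as not effective.* Worded this way it also covers death in the first 60 minutes. Add a sensitivity analysis that keeps the present definition.

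**List.** Before unblinding, replace the examples in SAP 6.1 with a closed list. For each agent named in protocol 4.2.1 and 7.2.2, including idarucizumab and andexanet alpha, and for cryoprecipitate, state whether it counts. Where routine and non-routine use are to be treated differently, as may be wanted for antifibrinolytics, define both. State that re-exploration means for bleeding or tamponade. Keep P1's rule for repeat dosing within 60 minutes: an entry that failed patients for any second dose would override it and turn P1 into S9.

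**Cost.** This is SAP wording plus one extra analysis. Deaths, IMP start times and the timing of products are already to be collected. Confirm that the clock time of early deaths and the reason for re-exploration are held, since the documents do not say so. The downside is a slightly lower response rate, and a death unrelated to bleeding will count as a failure; the sensitivity analysis shows how much that matters.
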